
(f). To assess if stricter volume control in fluid-overloaded patients (using UCR, UTR or conventional hemodialysis) affects quality of life measures. The secondary outcome measures for objective (g) are the mental component summary (MCS) and physical component summary (PCS) derived from the Kidney Disease Quality of Life Short Form (KDQOL-SF^TM^) [48]. The scale of both summary scores is 0 to 100 (higher indicating better quality of life). MCS and PCS in both groups, UCR and UTR, at time zero and at the end of study phase 1, will be compared against the conventional hemodialysis group, and afterward against one another, using the two-sided Student’s *t* test. The individual change in these parameters, from time zero to the end of study phase 1, will be compared likewise.

(g). To demonstrate superiority of UCR and/or UTR over conventional hemodialysis in reducing dialysis complications when previously fluid-overloaded patients are entering phase 2 and phase 3 of the presented study. In study phases 2 and 3, patients either have to reduce their dry weight further, or else have to maintain their newly reached dry weight. The secondary outcome measures for objective (h) are potentially all of the items described here above, and will be compared against the conventional hemodialysis group, and afterward against one another, in the same fashion as described here above.

(h). To assess which hemodialysis treatment modality will be chosen by the patients at the end of the study. The choice of treatment will be compared as follows: (1) number of patients choosing UCR treatment against number of patients choosing conventional treatment; (2) number of patients choosing UTR treatment against number of patients choosing conventional treatment; (3) number of patients choosing UCR treatment against number of patients choosing UTR treatment. The statistical test for analyses (1), (2) and (3) will be the two-sided chi square test, for each analysis.

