#### Superiority definition

For all objectives listed, superiority will be assumed if a statistically significant difference between one group versus another group can be determined. The significance level (alpha) will be set at 0.05. With regard to the primary endpoint, according to our sample size calculation (see below), this study is suited to detect a minimal difference of 10% between groups, if the occurrence of intradialytic symptoms in the conventional group is similar as in a previous study [20].

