Baseline is defined as the day of the BCM measurement. Time zero is defined, for every study phase, as the first hemodialysis session with dry weight reduction after the run-in phase. After completion of the first study period (twelve hemodialysis sessions for all three groups), patients crossover to the respective other study arms, as prespecified at the time of randomization. There is no explicit washout period between the first study phase and any of the subsequent study phases. However, another run-in period is required for the nonconventional treatment arms, before study phases 2 and 3. BCM measurements to adjust or re-prescribe dry weight reduction will be performed before every run-in period, and shortly before time zero of every study phase. If there is reason to believe that patients may have a change in their dry mass during the study period (for example, patients who are hospitalized or who change their diet), BCM measurement will be repeated, and the dry weight adjusted accordingly.

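### Objective (g) keeps a superiority aim and significance rule for phases 2 and 3, although the fluid left at the start of those phases depends on the preceding arm and the Study design section calls the comparison exploratory

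*Protocol article*

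**What the plan says.** All references are to the protocol article.

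- **Objectives and outcome measures, objective (g).** The aim is for UCR and/or UTR to be shown superior to the conventional arm "in reducing dialysis complications when previously fluid-overloaded patients are entering phase 2 and phase 3 of the presented study". In those phases "patients either have to reduce their dry weight further, or else have to maintain their newly reached dry weight". The outcome measures "are potentially all of the items described here above, and will be compared against the conventional hemodialysis group", and then the two techniques against each other, "in the same fashion as described here above". For continuous outcomes that means the two-sided t test used for phase 1. The outcome sentence names objective (h), but the lettering there is shifted by one and it stands under (g).
- **Superiority definition.** "For all objectives listed, superiority will be assumed if a statistically significant difference between one group versus another group can be determined", at alpha 0.05. Objective (g) is not exempted.
- **Study design.** The crossover serves (g) and (h) in exploratory form only. A meaningful crossover analysis is said to require a return to fluid overload, which was judged unethical.
- **Statistical analysis plan.** All secondary analyses are exploratory, and the primary analysis uses phase 1 only.
- **Study setting and organizational details.** Patients move on to the arms they have not yet had. "There is no explicit washout period between the first study phase and any of the subsequent study phases". BCM is repeated before each run-in and "shortly before time zero of every study phase", to adjust or re-prescribe the dry weight reduction.
- **Dry weight reduction.** Steps are halved after a first and second complication, with a 200 g floor, and reduction can end for that phase after a third.

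**The concern.** A patient's task in phase 2 or 3 is set partly by what the previous technique achieved. Someone who reached final dry weight only maintains it; someone whose reduction was slowed or stopped still has fluid to lose. Because no arm follows itself, phase-2 conventional patients come only from UCR or UTR, and phase-2 UCR patients only from UTR or conventional. If the trial's hypothesis is right, and objective (b) expects lower weights with UCR and UTR, the phase-2 groups differ at the start for reasons unrelated to current treatment.

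The same comparison is thus called exploratory in one section and given a superiority aim and a decision rule in two others. Followed literally, the rule could declare superiority from carry-over, most plausibly on relative weight reduction.

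**Working it through.** **The plan's own figure.** No figure is given for (g). The sample size statement concerns the phase-1 primary endpoint: difference 0.10, SD 0.10, two-sided alpha 0.05, power 0.80. The normal approximation gives 2 × (1.960 + 0.842)² × (0.10/0.10)² = 15.7, so 16 per group. The exact t calculation gives power 0.781 at 16 and 0.807 at 17, so the stated 17 is reproduced. It does not bear on the defect but gives a yardstick: the standard error of a difference is 0.10 × √(2/17) = 0.034, or 3.4 percentage points.

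**The mechanism by hand.** Take a 70 kg patient: the step is 0.1 kg per 10 kg, so 0.7 kg. Assume 4 kg to remove (not in the article).

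- No complications: 5 × 0.7 = 3.5 kg after five sessions and the last 0.5 kg in the sixth. Left at phase end: 0 kg.
- Complications in sessions 2, 4 and 6: session 1 removes 0.7; session 2 is reversed; session 3 removes 0.35 (total 1.05); session 4 is reversed; half of 0.35 is 0.175, so the 0.2 floor applies and session 5 brings the total to 1.25; session 6 is reversed and reduction ends. Left: 4 − 1.25 = 2.75 kg.

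A technique that prevents complications therefore changes the next phase's starting point.

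**Starting gaps under assumed risks.** Simulation of the step rule for a 70 kg patient over 12 sessions. Assumed, not in the article: UCR and UTR identical, all six sequences balanced, complication risk per reduction session as shown. Mean kg left at the start of phase 2, conventional vs UCR/UTR:

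| Risk, conventional / regulated | 4 kg at entry | 6 kg at entry |
|---|---|---|
| 0.14 / 0.04 | 0.12 vs 0.39 | 0.6 vs 1.2 |
| 0.30 / 0.20 | 1.1 vs 1.4 | 2.5 vs 3.0 |
| 0.45 / 0.20 | 1.1 vs 1.8 | 2.5 vs 3.5 |

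Balancing sequences does not remove the imbalance. With 6 kg at entry it shrinks by phase 3: 0.01 vs about 0.06 kg at 0.14/0.04, and 0.67 vs about 1.6 kg at 0.45/0.20.

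**Carry-over alone.** Here all arms have identical risk in phase 2, so any difference is carry-over. Assumed: UCR halves risk in phase 1, UTR performs like conventional, six sequences, 2, 3 or 5 kg to remove on average, session risk 10% (maintenance) to 30% (full step), or 14% to 50%.

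- 3 kg, lower risk: UCR starts phase 2 with 0.63 kg left, conventional with 0.42 kg. Relative weight reduction is 0.83% vs 0.55%, a ratio of 1.5; (0.83 − 0.55)% × 70 kg = 0.2 kg.
- Across scenarios the ratio is about 1.2 to 1.7, and complication sessions run about 0 to 2 points higher with UCR.

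**Sensitivity to sequence.** With three cyclic sequences (UCR–UTR–conventional and its rotations), all phase-2 UCR patients come from conventional. Two identical techniques then differ by about 0.2 to 4 points of complication sessions when maintenance risk is 25% to 50% of reduction risk. At 0.14/0.04 the difference is at most 0.6 points. If maintenance and reduction sessions carry equal risk, the complication bias is nil, but the starting gaps remain.

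**The case against.** The strongest reply is that the protocol discloses all this. The Study design section gives the reason itself, labels (g) exploratory and takes the crossover out of the primary analysis; the Statistical analysis plan section repeats the label for every secondary endpoint. A reader might infer that the authors overlooked carry-over or that the main result is compromised. Neither is supported.

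The size is also modest. With all six sequences, 0 to 2 points compares with a 10-point target difference and a standard error of 3.4 points, and the assumed full-step risks of 30% and 50% lie well above the planning rate of 0.14. The complication bias, on which (g) is chiefly worded, runs against the better technique when sequences are balanced, so it makes superiority harder to declare. The article also expects that, in theory, most patients could lose all excess fluid in one phase, which would shrink the effect.

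These points lower the severity, and all stand. They do not remove the conflict. An exploratory label reduces the weight of a result but does not correct a directional bias, and objective (g) and the superiority rule do not carry the label. Repeating BCM updates the target without equalising the distance to it. Nor is the matter simply left to an unseen analysis plan: the article itself fixes both the comparison and the decision rule.

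**Conclusion.** The point holds as an inconsistency with a real, directional consequence, of minor to moderate severity. The article keeps a superiority aim and a significance rule for a comparison that it elsewhere says cannot be a meaningful crossover analysis.

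If one technique works better in phase 1 and sequences are balanced, relative weight reduction in later phases is biased towards that technique and complications slightly against it. Weight reduction is defined under objective (b) for phase 1 only; it reaches phases 2 and 3 through the open-ended outcome list in (g). The complication bias needs maintenance sessions to be less risky than reduction sessions.

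No single size can be given. Sequences, session risks and kilograms to remove are not in the article, and it states no SD for weight reduction, so a false-positive rate cannot be computed. The simulated figures are illustrations. A reader might also infer that adding covariates would rescue the comparison. It would not: the starting gap arises after randomization, and with three cyclic sequences the preceding arm is fully determined by the current arm within phase 2. The phase-1 primary analysis is untouched.

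**What to change.** 1. Reword (g) so that it describes outcomes in phases 2 and 3 instead of seeking to show superiority.
2. Exempt (g) from the rule under Superiority definition, in line with the Study design section.
3. Report phases 2 and 3 descriptively by preceding arm and by the BCM fluid overload, or distance to final dry weight, measured shortly before time zero of each phase. State the sequences used. If they are the three cyclic ones, each phase-2 arm has only one preceding arm, and the report should say so.
4. Do not use relative weight reduction in phases 2 and 3 as evidence of superiority.
5. Label any analysis adjusted for the starting gap as a sensitivity analysis that does not restore a randomized comparison.

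The cost is wording and tabulation of data already planned; trial conduct does not change. The downside is that (g) supports a weaker claim. Cells are also small: with six balanced sequences, about 60/6 = 10 patients per combination of preceding and current arm in phase 2, before drop-out.

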#### Superiority definition

For all objectives listed, superiority will be assumed if a statistically significant difference between one group versus another group can be determined. The significance level (alpha) will be set at 0.05. With regard to the primary endpoint, according to our sample size calculation (see below), this study is suited to detect a minimal difference of 10% between groups, if the occurrence of intradialytic symptoms in the conventional group is similar as in a previous study [20].

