### Objectives and outcome measures

The primary objective is to demonstrate superiority of ultrafiltration and dialysate conductivity regulation (UCR) and/or ultrafiltration and temperature regulation (UTR) over conventional hemodialysis, in preventing intra- and post-dialytic complications, when fluid-overloaded hemodialysis patients receive systematic fluid reduction, to reach a final dry weight of normohydration weight −7% of ECW postdialysis. The primary outcome measure is the total number of hemodialysis sessions per patient that were accompanied, intra- or post-dialytically, by at least one symptom most likely related to fluid withdrawal (as specified in Table1), divided by the number of hemodialysis sessions at risk (as by study protocol: 12 sessions per patient in study phase 1). Both groups, UCR and UTR, will be compared against the conventional hemodialysis group, and afterward against one another, using the two-sided Student’s *t* test

**Table 1 T1:** Complications related to fluid withdrawa

(1)	Intradialytic cramping
(2)	Intradialytic hypotension (>40 mmHg SBP) within 30 minutes: clinically asymptomatic
(3)	Intradialytic hypotension (>40 mmHg SBP) within 30 minutes: clinically symptomatic
(4)	Clinically symptomatic intradialytic hypotension: unspecified drop in SBP
(5)	Unspecified intradialytic complication, most likely related to fluid withdrawal
(6)	Patient-reported postdialysis complication, most likely related to fluid withdrawal

The secondary objectives are:

(a). To demonstrate superiority of ultrafiltration and dialysate conductivity regulation (UCR) and/or ultrafiltration and temperature regulation (UTR) over conventional hemodialysis, in preventing specific intradialytic complications:when fluid-overloaded hemodialysis patients receive systematic fluid reduction, to reach a final dry weight of normohydration weight −7% of ECW postdialysis. The secondary outcome measure for objective (a) is the total number of hemodialysis sessions per patient which were accompanied by the respective symptom most likely related to fluid withdrawal (1 to 6), divided by the number of hemodialysis sessions at risk (as by study protocol: 12 sessions per patient in study phase 1). Both groups, UCR and UTR, will be compared against the conventional hemodialysis group, and afterward against one another, using the two-sided Student’s *t* test.

1. intradialytic cramping

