### Statistical analysis plan

The statistical analysis plan (SAP) provides full details regarding the analyses, the data display, and the algorithms to be used for data derivations. The SAP includes the definition of major and minor protocol deviations, which will be identified by medically trained staff before the study closure. Safety and tolerability are analyzed descriptively. Safety analysis is performed on the intention-to-treat (ITT) population. All secondary endpoint analyses are exploratory in nature.

Sample size calculation: for the primary endpoint analysis, we will assess the differences in intradialytic complications between the three study groups, only during the first study phase. Based on a typical occurrence of 0.14 dialysis-related complications per patient-day at risk in the conventional hemodialysis group [20], two-sided testing and an expected standard deviation of 10%, an alpha = 0.05 and a beta = 0.2, a sample size of 17 patients per group was determined to detect a minimum difference of 10% between groups. The UCR and UTR groups will be tested against the conventional hemodialysis control group, and afterward against one another. We expect a drop-out rate of approximately 10%. Individuals who do not complete the study cannot be replaced, because we do not include patients with hemodialysis vintage <3 months, and all patients who qualify for the study are asked to participate after the initial BCM measurement at all three centers. Thus, the study sample was determined to consist of 60 patients with ECW ≥15%, by BCM measurement. If patients are lost to follow-up, they will be excluded from the analysis

Two different analysis sets are defined for safety and efficacy, respectively. The efficacy of UCR and UTR will be assessed in all subjects who received the study method (at least once) and did not violate the protocol in a way that might affect the evaluation of the effect of the study method on the primary objective, that is, without major protocol violations. The per-protocol set is employed in the analysis of efficacy variables. The safety analysis set includes subjects who were randomized and received at least one study method (modified intention-to-treat). The safety set is employed in the analysis of tolerability and safety variables. Statistical analysis is performed with SAS.

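### The superiority rule lets any of three unadjusted pairwise t tests at 0.05 decide a 'UCR and/or UTR' objective, so 0.05 is not the error rate of the primary claim; the same rule conflicts with the exploratory status of the secondary endpoints

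*Protocol article*

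**What the plan says.** Under 'Objectives and outcome measures' the primary objective is met by either technique: "The primary objective is to demonstrate superiority of ultrafiltration and dialysate conductivity regulation (UCR) and/or ultrafiltration and temperature regulation (UTR) over conventional hemodialysis". The testing scheme follows: "Both groups, UCR and UTR, will be compared against the conventional hemodialysis group, and afterward against one another", each time by two-sided Student's t test. That makes three pairwise tests on the primary outcome.

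'Superiority definition' gives the decision rule, "For all objectives listed, superiority will be assumed if a statistically significant difference between one group versus another group can be determined", and its level, "The significance level (alpha) will be set at 0.05".

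The article's 'Statistical analysis plan' section repeats the scheme, "The UCR and UTR groups will be tested against the conventional hemodialysis control group, and afterward against one another", and sizes the trial on one unadjusted comparison: "an expected standard deviation of 10%, an alpha = 0.05 and a beta = 0.2, a sample size of 17 patients per group was determined". The same section says of everything else: "All secondary endpoint analyses are exploratory in nature". 'Study design' also describes the analysis of secondary endpoints (g) and (h) as exploratory.

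**The concern.** When an objective can be met in more than one way and each way is tested at 0.05, the chance of meeting it by accident exceeds 0.05. Nothing in the text offsets this. The word *afterward* puts the UCR versus UTR test later in time but does not make it depend on the earlier results. No split of alpha, order with a stopping condition, or overall test is given.

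At stake is what a positive primary result means: a reader would take 0.05 as the error rate of the trial's claim about the two techniques.

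The rule is also written for every listed objective. A significant secondary result would count as superiority under one section and as exploratory under another.

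**Working it through.** **Inputs (Protocol article).** Three arms, 1:1:1; two-sided tests; alpha 0.05; difference 10 points; SD 10 points; power 0.80; 17 per group; 60 patients in total (20 per arm); drop-out about 10%, leaving 20 × 0.9 = 18 per arm.

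**Step 1: the plan's own figure.** The standardized difference is 10/10 = 1. The noncentral-t calculation at two-sided 0.05 and 80% power gives 16.7, so 17 per group (power 80.7%). The stated size is reproduced, and it contains no allowance for multiple comparisons. The same calculation gives 83% at 18 and 87% at 20 per arm.

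**Step 2: primary error rate with no effect.** For the two comparisons with conventional, P(at least one) = 0.05 + 0.05 − P(both). The tests share the control arm, so P(both) is not 0.05² and was obtained by simulation: 200,000 null trials per arm size, normal data, equal variances, 17, 18 and 20 per arm.

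| Event | Probability |
|---|---|
| UCR or UTR differs from conventional, either direction | about 9% |
| UCR or UTR better than conventional | about 4.6% (4.5% to 4.6% across runs) |
| One such test alone, favourable direction | 0.05/2 = 2.5% |
| Any of the three pairs, either direction | about 12% |
| Any of the three pairs, gated by the overall F test at 0.05 | 5.0% |
| Either comparison with conventional, Holm over the two | about 4.6% |

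The large-sample studentized-range value for three pairs is 12.2%, which agrees. Three independent tests would give 1 − 0.95³ = 14.3%, an upper figure because the tests share arms.

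**Step 3: cost of control.** Power per comparison for a 10-point effect with SD 10:

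| Per arm | Unadjusted | F gate, third arm equal to one of the others | F gate, third arm midway | Holm over two |
|---|---|---|---|---|
| 18 | 83% | about 79% | about 73% | about 74% to 80% |
| 20 | 87% | about 84% | about 78% to 79% | about 79% to 84% |

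Holm is lowest when the third arm has no effect, where it is close to Bonferroni at 0.025 (74% and 79%). It is highest when both techniques work.

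**Step 4: secondary tests written into the objectives.**
- (a) 6 symptoms × 3 pairs = 18
- (b) 3
- (c) 3
- (d) 5 markers × 3 (time zero, end, change) × 3 pairs = 45
- (e) 7 named markers × 3 × 3 = 63
- (f) 2 scores × 3 × 3 = 18
- (h) 3

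The sum is 153. Time-zero comparisons number (5 + 7 + 2) × 3 = 42, leaving 153 − 42 = 111. With no true effects, 111 × 0.05 = 5.6 would be significant by chance. Of the 111, only 18 + 3 = 21, in (a) and (b), belong to objectives worded as demonstrating superiority: 21 × 0.05 = about 1. Objective (g), also worded that way, may repeat the items in phases 2 and 3 and is not counted.

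**The case against.** The strongest reply has four parts.

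*The hypothesis concerns conventional hemodialysis only.* This stands. UCR versus UTR is in neither the hypothesis nor the primary objective. A reader might infer that the trial's main claim carries a 12% error, or that a false win over conventional is twice as likely as 0.05. The documents support neither: 12% needs the third pair and both directions, and a false win over conventional occurs in about 4.6% of null trials. That is still nearly double the 2.5% that one two-sided 0.05 test allows in that direction. The superiority rule as worded also does not exclude the third pair.

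*Secondary analyses are already exploratory.* This largely stands. A reader might infer about 150 planned superiority claims. The 153 includes 42 time-zero comparisons, which cannot show a treatment benefit, and most objectives are worded as assessing, not demonstrating. What remains is a contradiction between two sections.

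*Multiplicity belongs in the separate analysis plan.* That plan is not shown and may contain an adjustment. But the article itself fixes the decision rule and sizes the trial at an unadjusted 0.05, so an adjustment elsewhere would contradict this text.

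*Adjustment for distinct treatments sharing a control is debated.* True in general. Here a single objective is met by either technique, which is the case where joint control is easiest to justify.

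**Conclusion.** The point holds in this limited form. Under the written rule, 0.05 is not the error rate of the primary claim. It is about 9% for the two comparisons with conventional (about 4.6% in favour of a technique, against 2.5% for one test) and about 12% only if UCR versus UTR counts too. These figures assume normal data, equal variances, equal arms of 17 to 20, and no effect of either technique.

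The secondary part is a conflict of wording: one section extends the superiority rule to all objectives, another calls all secondary analyses exploratory. It does not put the primary conclusion at risk.

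**What to change.** Before any analysis, choose one of two rules and write it into 'Superiority definition' and the analysis section:

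1. Interpret the three pairwise tests, each at 0.05, only if the overall three-group F test is significant at 0.05. With exactly three groups this holds the family-wise error at 5%.
2. Apply Holm to the two comparisons with conventional (smaller p value against 0.025; if that is significant, the larger against 0.05), and label UCR versus UTR exploratory.

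The second follows the stated hypothesis more closely; the first keeps UCR versus UTR within the controlled family.

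Neither adds patients. The cost is power: at 18 per arm from 83% to about 73–79% (F gate) or 74–80% (Holm); at 20 per arm from 87% to about 78–84% or 79–84%, depending on the third arm. The sample-size paragraph should restate power under the chosen rule, since 80% is no longer assured at 18 per arm.

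Limit the superiority rule to the primary endpoint, reword secondary objectives (a), (b) and (g) to match, and report secondary results as estimates with 95% confidence intervals. This costs only wording.
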